### Analysis plan

We will conduct school-level and individual (cohort) level analysis. We will compare adolescents in the control and intervention schools to determine whether the health literacy intervention is associated with an increase in help-seeking. We will use non-randomised difference-in-difference (DID) analysis (34) to adjust for differences between schools (school-effects) and over time (time effects). The DID design is a quasi-experimental approach which enables the researcher to study causal relationships in settings where randomised control trials are unfeasible or unethical (35). Our outcomes are predominantly proportions (e.g., proportion seeking help), thus we will use a binomial-logistic regression model approach to estimate relative (odds ratios) and absolute (differences in proportions) effects of the intervention. The number of schools is likely too small to reliably estimate school-level random effects, so a mixed model is not considered. We will analyse our universal repeated assessments (administered to all adolescents in intervention and control schools) to determine the effects of the health literacy component on longitudinal mental and physical health measures (baseline, 8, 15, and 22 months). These data will be analysed using an individual level linear model with adolescent random effects, school, time and intervention fixed effects. We will conduct sub-analysis with the cohort of adolescents receiving counselling. The targeted cohort assessments (**Table 2**) will allow us to describe the trajectories of adolescents receiving the counselling component of the intervention to determine whether the counselling has an impact on mental and/or physical health outcomes. For the continuous cohort outcomes (“universal assessment”) the minimum detectable standardised effect size is approximately 0.1 assuming an individual autocorrelation coefficient between time periods of 0.8.

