Our sample size calculation is based on the proportion of adolescents seeking help in the control versus intervention groups. While epidemiological findings from LMICs show that approximately 8-10% of youths experience mental health problems requiring intervention, less than 1% receive help (36, 37). Since we are signposting adolescents in the control schools to local services, we anticipate that approximately 5% might seek help. For those receiving the ISOBAR intervention, we predict an increase in the proportion of adolescents who seek care (among those who reach the pre-defined threshold) from 5% (in control arm) to 11-12% (in intervention arm). We are planning to recruit three schools per site. Our sample size calculation assumes an increase in help-seeking of 6-7% in the intervention group compared to the control schools (i.e., 5 to 11-12%). Thus, if we recruit 200 adolescents per school, we will have 80-90% power to detect an improvement of at least 6–7 percentage points. Therefore, we plan to recruit a minimum of 200 adolescents per school per site: 200 x 3 = 600 adolescents per site (Total n = 1,800).

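### The assumed rise in help-seeking is defined among adolescents who reach the referral threshold, but the 80-90% power is attached to all 200 recruited per school

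*Protocol article*

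**What the plan says.** The sample size paragraph of the Analysis plan rests on the proportion of adolescents seeking help.

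- It cites background evidence that "approximately 8-10% of youths experience mental health problems requiring intervention", then says of control schools that "we anticipate that approximately 5% might seek help".
- It defines the expected effect as an "increase in the proportion of adolescents who seek care (among those who reach the pre-defined threshold) from 5% (in control arm" to 11-12% under intervention.
- It repeats the effect without the restriction: "Our sample size calculation assumes an increase in help-seeking of 6-7% in the intervention group compared to the control schools".
- It concludes that "if we recruit 200 adolescents per school, we will have 80-90% power to detect an improvement" of at least 6-7 percentage points, and so arrives at 600 per site and 1,800 in total.

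The comparison itself carries no threshold restriction. The Analysis plan states: "We will compare adolescents in the control and intervention schools to determine whether the health literacy intervention is associated with an increase in help-seeking". The first primary research question, under Objectives, aims, and research questions, concerns an intervention given to every adolescent in class. The section on effectiveness of the health literacy component likewise compares help-seeking between conditions without limiting it to adolescents above the threshold.

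**The concern.** An effect defined in a subgroup and a power figure attached to everyone recruited cannot both stand without a step that converts one into the other, and the paragraph has none. If the 5% to 11-12% applies only to adolescents who reach the threshold, the number that matters is the threshold-positive adolescents per school, not 200. If it applies to everyone, the bracketed restriction is wrong and the two proportions need confirming for that population.

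This paragraph is the only justification given for 1,800 participants, and it serves the first of the two primary research questions. As written, a reader cannot tell which population the 80-90% covers. A null result could then be taken as evidence of no effect when the comparison had much less power than stated.

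**Working it through.** **Inputs from the article.** Control 5%; intervention 11% or 12%; 200 per school; three schools per site and three sites; assessments at baseline, 8, 15 and 22 months; a model with school and time fixed effects and no school random effects.

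**Inputs assumed.** Two-sided alpha 0.05; roll-out 0111 / 0011 / 0001 for schools A, B and C over the four assessments (Figure 2 is not available to this review); independent observations; normal approximation.

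**Formula.** SE = sqrt(f × p̄(1 − p̄) / m), where m is the number per school at each assessment, p̄ is the mean of the two proportions, and f is the inverse of the sum of squares of the treatment indicator after removing school and time effects. Power = Φ(difference/SE − 1.96).

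- One site: sum of squares = 6 − 4(0.75² + 0.5² + 0.25²) − 3(0 + 1/9 + 4/9 + 1) + 12(0.5²) = 6 − 3.5 − 4.667 + 3 = 0.833, so f = 1.2.
- Three sites: 3 × 0.833 = 2.5, so f = 0.4.
- p̄(1 − p̄) = 0.08 × 0.92 = 0.0736 for 5 v 11%, and 0.085 × 0.915 = 0.0778 for 5 v 12%.

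**Step 1: the stated figure, all 200 per school counted.**

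- One site, 5 v 11%: SE = sqrt(1.2 × 0.0736/200) = 0.0210; 0.06/0.0210 − 1.96 = 0.90; power 81.5%.
- One site, 5 v 12%: SE = sqrt(1.2 × 0.0778/200) = 0.0216; 0.07/0.0216 − 1.96 = 1.28; power 90.0%.
- Three sites pooled: over 99% for either effect.

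The stated 80-90% is thus reproduced on a one-site basis.

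**Step 2: only threshold-positive adolescents counted.** The article gives no threshold-positive share. The only prevalence in the paragraph is 8-10%, for mental health problems requiring intervention; used as a proxy, it gives m = 16 to 20 per school.

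- One site: from SE = sqrt(1.2 × 0.0736/16) = 0.0743, power 12.5%, to SE = sqrt(1.2 × 0.0778/20) = 0.0683, power 17.5%.
- Three sites pooled: from SE = sqrt(0.4 × 0.0736/16) = 0.0429, power 28.7%, to SE = sqrt(0.4 × 0.0778/20) = 0.0394, power 42.7%.

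**Step 3: sensitivity, three sites pooled.**

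| Condition | Power, 5 v 11% to 5 v 12% |
|---|---|
| Share 20% (m = 40), independent | 60-71% |
| Share 30% (m = 60), independent | 77-87% |

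Within-person correlation ρ multiplies the variance by (1 − ρ). At a share of 8-10%, over both effects, the formula gives 51-71% for ρ = 0.5 and 88-98% for ρ = 0.8; a simulation of correlated binary data at 0.8 gives about 66-85%. The article states 0.8 only for continuous outcomes.

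**Step 4: the effect diluted over all adolescents.** If the gain occurs only above the threshold and the analysis includes everyone, the expected difference is 0.08 × 6 = 0.48 to 0.10 × 7 = 0.70 percentage points, against the 6-7 points assumed. This is a worst case, with no effect below the threshold.

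**The case against.** The strongest reply is that the restriction is a slip. The other sentences on the effect, the research question and the planned comparison speak of adolescents generally. If 5% and 11-12% are meant for all of them, 80-90% holds for one site under the assumptions above, and deleting the bracket removes the problem. That stands, and it is why deletion is the preferred fix. But the article has to say so: the 5% follows directly on a figure for youths with mental health problems, so its denominator is not self-evident.

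A reader might go further in three ways that the article does not support.

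- **That the true power is 29-43%.** This range needs an 8-10% share, and referral is on SDQ and/or BMI (Table 1 and the section on universal assessment and referral), so the share may be higher. It also rests on an assumed schedule and independent repeat assessments. Nor should it be set against 80-90%, which is reproduced per site, whereas 29-43% is pooled. The like-for-like contrasts are 81.5-90.0% against 12.5-17.5% (one site) and over 99% against 28.7-42.7% (pooled).
- **That the calculation demonstrably counted all 200.** No formula is given. A count of 9% of 3,600 v 3,600 person-assessments (324 v 324) gives 80.5% and 89.3%, nearly as good a match using threshold-positive adolescents. That route ignores school and time effects and repeated measures, so it would not support the stated power under the planned model, but it does mean the denominator used is inferred.
- **That 11-12% contradicts the referral of threshold-positive adolescents to counselling.** Being referred is not the same as reporting help sought in the past six months, which is the outcome in Table 1.

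It is also fair that alpha and the correlation may sit in a fuller document. The mismatch does not depend on them, because the article itself states the effect's population, the number recruited and the power.

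**Conclusion.** The sample size justification contradicts itself: the effect is defined among adolescents who reach the threshold, while the number recruited and the planned comparison cover all adolescents. The 80-90% is not an arithmetic error in itself, since it can be reproduced for one site with everyone counted. It does not follow if the restriction stands and the threshold-positive share is near 8-10%. Under independence, power is then about 13-18% for one site or 29-43% pooled. It approaches the stated range only with a share near 30% pooled, or with substantial within-person correlation. The existence of the mismatch is certain from the text; the size of any shortfall is conditional on the share, the schedule and the correlation, none of which can be read from the article for this outcome.

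**What to change.** Use one denominator for the effect, the sample size and the primary help-seeking analysis.

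- **Preferred:** delete the bracketed restriction to adolescents reaching the threshold, define the outcome as the proportion of all assessed adolescents who seek help, and confirm or restate 5% and 11-12% for that population.
- **Otherwise:** keep the threshold-positive denominator, restrict the primary analysis to it, state the expected share under the SDQ/BMI criteria, and replace 80-90% with the power at the resulting number. The 29-43% should not simply be printed in its place, because it depends on an assumed share.

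In either case, say whether the power is per site or pooled over the three sites, and what within-person correlation it assumes for help-seeking.

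The cost is a change of wording and a recalculation, with no extra recruitment. The downside is that the stated power may become less favourable.

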### Effectiveness of the health literacy component

We will estimate the effectiveness of the health literacy component of the intervention in the following ways: (1) through a comparison of the proportion of adolescents seeking help in the intervention versus the control conditions; (2) by assessing impacts on knowledge, attitudes, and behaviour; and (3) by assessing impacts on nutritional (e.g., body mass index, dietary behaviours) and mental (e.g., Strengths and Difficulties Questionnaire) health. These outcomes will be assessed at three follow-up time points: 8, 15 and 22 months.

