### Objectives, aims, and research questions

The main aim of ISOBAR is to develop and test the effectiveness and implementation of a school-based three-stage (assessment and referral, universal health literacy, and indicated counselling) composite physical and mental health intervention in India (Chennai and Gujarat) and Nigeria (Ibadan).

Key objectives include:

To co-develop and culturally adapt a universal health literacy intervention combining mental and physical health modules.To assess all adolescents for emotional, behavioural, and nutritional/weight problems using validated assessment tools.To develop, and culturally adapt, an indicated counselling intervention for adolescents reaching pre-determined thresholds on the above universal assessment indices.To implement and evaluate the school-based intervention at each site using quantitative and qualitative implementation assessment tools.To assess the costs of the intervention and explore how these relate to consequences and affordability.To estimate the effectiveness of the school-based intervention (health literacy and counselling components) with a suite of outcome measures, including help-seeking, mental health symptoms, diet and activity, and anthropometric measures.

We have two primary research questions:

Does a health literacy intervention (delivered to all adolescents at classroom level) increase help-seeking behaviours?Do adolescents who receive counselling for physical and/or mental health problems experience improved outcomes?

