#### (1) Universal assessment and referral

We selected assessment tools to measure mental health and behavioural problems (Strengths and Difficulties Questionnaire: SDQ; Global School-Based Student Health Survey: GSHS), well-being (WHO-5 well-being index), nutritional problems, and at-risk weight status (Body Mass Index: BMI) Tools selected were: (1) relatively quick to administer; (2) well-established; (3) previously used and validated in our study countries; and (4) available in the local language. We will also assess help-seeking behaviour and health literacy with bespoke scales. The health literacy scale will draw on the conceptual framework developed by Jorm (27) and capture key components of the intervention (e.g., beliefs about the utility of counselling, stigma surrounding mental illness). Assessment scales are self-report and will be completed by adolescents at baseline, 8, 15 and 22 months with support from trained research assistants. Weight, height and arm circumference measurements will be recorded by researchers. All adolescents (in control and intervention schools) will be assessed. Adolescents in the intervention school reaching the pre-determined threshold on either the SDQ and/or the BMI (**Table 1**) will be referred to the inhouse counselling intervention. Adolescents in the control schools who are identified through the universal assessments as having potential mental health or nutritional concerns will not be left without support. All participants with such concerns will be informed of their screening results in an age-appropriate manner. Where necessary, efforts will be made to inform parents or guardians through the school system, in line with ethical and safeguarding procedures. Participants and their families will be advised to seek appropriate care, and the research team will facilitate this by providing information on available services, including referral pathways to specialist mental health care.

**Table 1 T1:** Universal assessments administered to all adolescents in intervention and control schools.

Name of scale/assessment	Description	Items in scale	Threshold for referral to counsellor	Time-points
Socio-demographic questionnaire	Bespoke scale assessing key demographic factors (culturally adapted for each site)	Age, gender, religion, parents’ education level, family size and composition, geographical setting	N/A	Baseline

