Help-seeking behaviour questionnaire	Bespoke scale assessing help- seeking	Sought help in the past six months, frequency of help- seeking, and who from/what for	N/A	Baseline, 8, 15, 22 months
Health literacy	Bespoke scale based on Jorm (27) conceptual framework	Example items: Ability to give advice, how to improve well-being, thoughts on counselling, stigma, knowledge of mental illness	N/A	Baseline, 8, 15, 22 months
Strengths and Difficulties Questionnaire (SDQ)	Validated scale to assess emotional and behavioural issues	• Emotional symptoms • Conduct problems • Hyperactivity/inattention • Peer problems • Prosocial behaviour	• Based on algorithm (hierarchical): -Very high score/very high impact - High score/very high impact -Very high score/high impact -High score/high impact (Impact score is given more weight)	Baseline, 8, 15, 22 months
WHO-5 well-being index	Validated measure of well-being	• Cheerful/good spirits • Calm and relaxed • Active and vigorous • Fresh and rested • Things that interest me	N/A	Baseline, 8, 15, 22 months
Global School-Based Student Health Survey (GSHS)	Validated scale for adolescents to assess risks for morbidity and mortality	• Dietary behaviours • Drug use • Hygiene • Mental health • Physical activity • Sexual behaviours • Drug use • Tobacco use	N/A	Baseline, 8, 15, 22 months
Body Mass Index (BMI)	Screening tool for weight-related health risks	• Weight in kg • Height in metres^2^	Sites will follow country specific thresholds for overweight and obesity	Baseline, 8, 15, 22 months

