**Figure 2 f2:**
[figure not shown]
A schematic view of intervention delivery at Chennai, Gujarat, and Ibadan. There are three schools (A, B, C) per site; universal assessments are conducted at four time-points (baseline, 8 months, 15 months, 22 months); dark green box represents delivery of universal health literacy; light green box represents delivery of counselling intervention.

The intervention will be delivered in two stages: (1) all adolescents in the intervention school will receive the health literacy component (dark green box); (2) a subset of adolescents in the intervention school will receive the counselling component if they meet the pre-defined threshold indicating nutritional/weight and/or mental health problems (light green box). These adolescents will comprise the sub-cohort who will be followed up at two/three and 12 months. Once the counsellors are introduced into each school, they will remain for the duration of the study.

Each study site will have three schools (school A, B and C) who will receive the intervention in a staggered manner so that each of the three schools will eventually receive the intervention. Schools will initially serve as the control condition and then incrementally transition to the intervention phase. Therefore, while schools function as the control condition at specific time points, there are no fixed “control schools.” We do not consider contamination to be an issue in this design because students will not switch schools, and counsellors are assigned to a school each.

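### The intervention-versus-control contrasts are presented as effects of health literacy, but the intervention condition also brings referral to an in-school counsellor, so as written they estimate the whole programme

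*Protocol article*

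**What the plan says.** All references are to the Protocol article.

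- **Question.** Objectives, aims, and research questions asks: "Does a health literacy intervention (delivered to all adolescents at classroom level) increase help-seeking behaviours". Counselling is the subject of a separate, second primary question.
- **Contrast.** Effectiveness of the health literacy component says that component will be evaluated "through a comparison of the proportion of adolescents seeking help in the intervention versus the control conditions". It also lists knowledge, attitudes and behaviour, and nutritional and mental health measures including BMI and the SDQ. On timing it says: "These outcomes will be assessed at three follow-up time points: 8, 15 and 22 months". The Analysis plan makes the same attribution for help-seeking and for the repeated measures in all adolescents.
- **Outcome.** Table 1 describes the help-seeking questionnaire as: "Sought help in the past six months, frequency of help- seeking, and who from/what for".
- **What else intervention-condition schools receive.** Under (1) Universal assessment and referral: "Adolescents in the intervention school reaching the pre-determined threshold on either the SDQ and/or the BMI" ... "will be referred to the inhouse counselling intervention". Section (3) Indicated counselling places the start of in-school counselling within a month of the initial assessment, and also opens it to adolescents who do not screen positive on the SDQ but ask for help. Phase 2, below Figure 2, adds: "Once the counsellors are introduced into each school, they will remain for the duration of the study".
- **What control-condition schools receive.** Adolescents with concerns are told their screening results, families are informed where needed, and information on local services and referral pathways is given.
- **Model.** For the longitudinal outcomes the Analysis plan describes one intervention term, with school and time terms and a random effect for adolescent.
- **Planning figures.** The sample size paragraph uses 8-10% needing intervention, 5% seeking help in the control condition and 11-12% in the intervention condition. It words the rise as applying to adolescents over the referral threshold.

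**The concern.** The literacy question can be answered by an intervention-versus-control contrast only if literacy is what separates the conditions, or if the outcome or model removes the rest. Here referral and an in-school counsellor arrive in the same schools. An adolescent who attends because the study referred them could report help in the past six months even if the classroom sessions changed nothing. Similarly, the adolescents with high SDQ or BMI values are the ones referred, so counselling can move the all-adolescent SDQ and BMI results. That second problem does not depend on how help-seeking is coded.

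At stake is the first primary conclusion. A statement that classroom literacy raises help-seeking could rest partly or wholly on referral and counselling, and schools might then adopt the classroom component alone on that evidence. The Highlights disclose two limitations, the lack of randomisation and dilution by signposting in the control condition. Neither covers this bias, which would exaggerate the apparent literacy effect.

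**Working it through.** **1. The plan's own figure.** The article states 80-90% power for 5% versus 11-12% with 200 adolescents per school. It gives no alpha, sidedness, clustering allowance or number of observations per condition, so the figure cannot be reproduced exactly. With two-sided alpha 0.05 (assumed) and no clustering, power for 11% / 12% is 60% / 71% with 200 per condition, 77% / 87% with 300, and 97% / 99% with 600. This does not decide the present point; it shows only that the basis of the planning rates is not explicit.

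**2. What separates the conditions.**

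| Element | Intervention condition | Control condition |
|---|---|---|
| Universal assessment | yes | yes |
| Screening feedback and signposting | superseded by referral | yes |
| Classroom literacy | yes | no |
| Referral to in-school counsellor | yes | no |
| Counsellor in school to the end | yes | no |

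Literacy, referral and the counsellor differ together. One intervention term cannot apportion an effect among them.

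**3. Can study counselling fall inside the outcome window?** A six-month look-back at 8, 15 and 22 months covers roughly months 2-8, 9-15 and 16-22. Counselling may be continued as needed and the counsellor remains, so sessions can fall inside these windows. Brief early counselling could fall outside them.

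**4. Illustration with a literacy effect of exactly zero.** Inputs: background b = 5% and referred share q = 8-10%. The latter is the article's figure for need, used as a stand-in because no screen-positive rate is given; BMI referrals could raise it. The share u who attend and report it as help is assumed, because the article gives no uptake.

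- Case A, background seeking independent of screening: p = b + q × u × (1 − b). For example, 0.05 + 0.08 × 0.50 × 0.95 = 8.8%.
- Case B, every background seeker is screen-positive: p = b + (q − b) × u. For example, 0.05 + (0.10 − 0.05) × 1.00 = 10%.

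| Uptake u | Case A, q = 8% | Case A, q = 10% | Case B, q = 8% | Case B, q = 10% |
|---|---|---|---|---|
| 50% | 8.8% | 9.8% | 6.5% | 7.5% |
| 75% | 10.7% | 12.1% | 7.3% | 8.8% |
| 100% | 12.6% | 14.5% | 8.0% | 10.0% |

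In case A, a rate of 11-12% is reached at u = (0.06 to 0.07) / (0.08 × 0.95) = 79-92% for q = 8%, and (0.06 to 0.07) / (0.10 × 0.95) = 63-74% for q = 10%. In case B it is not reached. If study-arranged contacts are excluded, both cases give 5% versus 5%.

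**5. Denominator.** These are rates in all adolescents. The article words its 11-12% as a rate among those over the threshold. If study counselling counted in that group, the rate would be at least u. With b = 5% independent of attendance, 11-12% would imply u of only 0.06 / 0.95 = 6.3% to 0.07 / 0.95 = 7.4%. The figures in step 4 therefore cannot be set against the planned rise until the denominator is settled.

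**The case against.** A reader might infer that the outcome does count study-assigned counselling, so that it must rise mechanically and the study cannot show a literacy effect. The documents do not support that.

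- No section says study counselling is counted. Table 1 records the source and reason for help, and (3) Indicated counselling treats asking for help as distinct from screening positive. Scoring of a bespoke item is a detail an article may leave to a fuller document.
- The planning rate, read literally among those over the threshold, fits poorly with counting study counselling (step 5).
- Delivery is in two stages and Figure 2 is not shown, so an assessment falling after literacy but before counselling cannot be ruled out.
- The control condition is more than posters. Screening feedback and referral information can prompt help-seeking there too.
- Knowledge and attitudes are also measured and lie closer to the literacy component.

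All of this stands against the strong reading, and it shows that a separation is feasible. It does not answer the narrower point. The article assigns the contrast to literacy in its own words, uses all three follow-ups without restricting them to a literacy-only period, and does not turn the source item into an outcome rule. The SDQ and BMI attribution is untouched by any argument about coding help-seeking.

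**Conclusion.** The point holds as one of attribution. The Analysis plan and the section on the literacy component credit that component with contrasts in help-seeking, SDQ and BMI that belong to the three-part programme. Unless study-arranged counselling is excluded, the help-seeking contrast cannot isolate literacy.

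With no literacy effect, the apparent rise in all adolescents could be about 4-5 points at 50% uptake and 6-7 points at 75% if background seeking is unrelated to screening. It would be at most 3-5 points, at full uptake, if all background seekers screen positive. These sizes rest on assumed uptake, on the 8-10% need figure standing in for the referred share, and on study counselling being reported as help within the look-back. They show that the bias could matter; they do not estimate it. A reader might infer that counselling alone would deliver the planned 6-7 points. That does not follow, because the planned rise is worded for a different denominator.

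**What to change.** 1. In the Analysis plan and in Effectiveness of the health literacy component, label the all-adolescent help-seeking, SDQ and BMI contrasts as effects of the whole ISOBAR programme.
2. For the literacy question, define help-seeking not arranged by the study, using the source-and-reason item already collected together with referral records. Apply the same rule in both conditions, so that contacts prompted by screening feedback in the control condition are treated like those prompted by referral. Report all-source help-seeking beside it.
3. Restate the 5% and 11-12% planning rates for the chosen definition, and say whether the denominator is all adolescents or those over the threshold.
4. Treat any analysis of below-threshold adolescents as supportive only. An in-school counsellor is available to them as well, so it is not a pure literacy contrast.
5. Reconcile the two descriptions of entry to counselling: SDQ and/or BMI threshold under (1) Universal assessment and referral, but SDQ or having sought help under (3) Indicated counselling. The classification in item 2 depends on it.

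The cost is mainly wording and an outcome definition, with no new questionnaire or design change. The event rate will be lower under the restricted definition. Some adolescents who would have sought help anyway will be classified as referred, which works against the intervention condition; the all-source result alongside makes that visible. Even then, the counsellor's presence stays bundled with literacy, so the restricted result should be described as closer to the literacy question, not as a clean answer to it.
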